### Recruitment procedure

Based on the results from preparatory studies, we developed a strategy to address and activate managers of MSE. We developed a joint communication strategy with cooperating recruitment partners (i.e., institutions and networks who support the occupational health and safety activities of MSE).

The first principle of this strategy is the digital distribution of information via email. The second principle of the strategy is cooperation with recruitment partners. Addressing employers of MSE via email is suitable, as it reaches a large sample with limited use of resources. Previous studies of the project show that employers typically obtain information on occupational health and safety topics from well-known networks and institutions, such as accident and health insurance companies. Hence, the access and communication strategy requires a close cooperation with these stakeholders (i.e. recruitment partners). We ask recruitment partners to contact MSE via email and inform them about the offer. Interested employers can follow a link to the project website, where they will learn about the advantages of stress prevention and “System P”. Each recruitment partner receives an individualized link, which allows a partner-specific analysis of the response behavior. Through the networks of our recruitment partners, we will be able to contact at least 1000 employers of MSE via email. As the recruitment partners will distribute the emails, the study team will not have access to any personal information prior to registration (e.g. names and email addresses).

Employers who fulfil the inclusion criteria will get access to the platform. They will also receive information about how to invite their employees to participate in the use of the platform. Both employers and employees can access the platform via personal accounts after a formal registration and acceptance of the terms and conditions for study participation and data protection. Employers of MSE that fulfil the inclusion criteria at registration (T0) but do not use the platform further (no login within 1 month) will be contacted again via email to fill out a short non-responder questionnaire about their socio-demographics and their reasons for not participating. To maximize the response rate, we will send a reminder via email for each questionnaire.

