#### Process outcomes

Acceptability: One measurement of acceptability of stress prevention interventions is the readiness for change which will be assessed by three items adapted from Hoek et al. [63]. Items are “I believe in the value of stress prevention”, “Stress prevention is positive for the organization” and “Stress prevention is necessary” and the answers range from 1 “strongly disagree” to 5 “strongly agree”. After the implementation period, we will also measure satisfaction with the intervention by asking participants to rank the usefulness of each intervention component at T2 on a 5-point scale, with a target average score of 3 or higher.

Adoption/Reach: The proportion of MSE who adopted “System P” will be calculated by dividing the number of registered MSE at T0 by the number of invited MSE during recruitment (R1). Reach will be analyzed by comparing socio-demographic characteristics of MSE that implemented “System P” with the characteristics of non-responders (using aggregated data from the recruitment partners and data from non-responder questionnaire) to see if they are representative of the population.

Appropriateness: To gain further information on appropriateness (perceived fit for the setting), we will conduct semi-structured personal interviews with employers of MSE that are registered with inter-corporate stakeholders who are unable to contact their members via email newsletters at R1 as described above. Employers will be contacted via phone by the recruitment partners and referred to the project team. They will receive access to videos sequences introducing the web-based platform in the week prior to the interview and will then be asked about aspects that they liked and disliked as well as potential barriers for the use of the platform (the interview guide can be found in Additional file 3). The platform should be regarded as appropriate by a majority of the employers.

Fidelity: To measure fidelity, we analyze usage data collected directly via “System P”. We will track data on the times of login, number of steps completed in the web-based tool for PRA (minimum 2) and the number of completed sessions in the web-based training (minimum 5). Additionally, we will ask the participants about their use of the interventions in the online questionnaires at T2 and T3 (e.g. “How much time have you spent on average for the training?”).

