### Analysis

#### Sample size

Power analysis has been performed with G*Power [66] for a one sample case on the primary outcome measure depressive symptoms (PHQ score). Based on the average changes in depression reported in previous research [19, 22], we estimate a medium effect size (Cohen’s d = 0.4) [67]. With a power of 0.95 and a one-sided alpha α of 0.05, this resulted in a sample size of *n* = 70 at post-intervention measurement (T2). Due to interdependencies of the observations within MSE, we multiplied n with the design effect (DE) of cluster-randomized trials (DE = 1+ (NC-1)*ICC) [68], assuming an average cluster size (NC) of 5 (average number of employees in German MSE) and an intra-class correlation coefficient (ICC) of 0.1. This results in a required sample size of *n* = 98, and a minimum number of 20 MSE. If only 2-person MSE register (NC = 2), this would result in a required sample size of *n* = 77, equaling 39 MSE. We cannot predict the actual size of the MSE (with a range from 1 to 49 employees) and how many MSE will complete post-intervention assessment (T2) but previous studies show that only one quarter of all MSE that start interventions for stress prevention complete them [69]. The goal is therefore to recruit between 80 and 150/200 MSE for the baseline measurement. In the case of more registrations, only the first 200 MSE will be considered for the subsequent analyses.

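### If more than 200 MSE register, the plan drops the later ones from analysis by order of registration, without a reason and at an avoidable cost in precision

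*Protocol article*

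**What the plan says.** The rule is in the protocol article under Sample size. It follows the recruitment target, "The goal is therefore to recruit between 80 and 150/200 MSE for the baseline measurement", and reads: "In the case of more registrations, only the first 200 MSE will be considered for the subsequent analyses". It gives no reason and does not say which analyses it covers.

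Four other places bear on it:

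- **Recruitment procedure** expects to reach "at least 1000 employers of MSE via email" and grants platform access to every employer who meets the inclusion criteria. It sets no ceiling on enrolment.
- **Study design** has the outcome questionnaires administered through the platform, and **Process outcomes** (Fidelity) draws usage data from it.
- **Process outcomes** (Adoption/Reach) defines adoption by "dividing the number of registered MSE at T0 by the number of invited MSE during recruitment (R1"), with no cap on the numerator.
- **Study limitations** expects few replies to the invitation emails and describes a back-up recruitment strategy in case of a shortfall.

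**The concern.** The sentence limits the analysis set, not enrolment. An MSE that registers as number 201 would use the platform and answer the questionnaires, and its answers would then be set aside. The article describes no interim look, allocation or other feature that needs a fixed maximum. The primary outcome is a within-person change in one sample, and extra MSE would simply sharpen that estimate.

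Two things would be at stake. The first is precision, both for the primary change score and for the comparison of people who completed the minimum steps with those who hardly started, which stands in for a control group and for which the article gives no power. The second is representativeness, because who is analysed would depend on when the employer registered. In a type 2 hybrid design the implementation outcomes rank equally with effectiveness, so it also matters that the wording leaves open whether adoption and reach fall under the cap.

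**Working it through.** **Inputs from Sample size.** "With a power of 0.95 and a one-sided alpha α of 0.05"; "we estimate a medium effect size (Cohen’s d = 0.4"); "assuming an average cluster size (NC) of 5", with 2 as the alternative; "intra-class correlation coefficient (ICC) of 0.1"; one quarter of MSE that start such interventions complete them. The number invited, 1000, comes from Recruitment procedure. **Assumptions made here to show a range:** 250 or 300 registrations, and one respondent per MSE (NC = 1).

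**Step 1. Reproduce the plan's figures.** A one-sample t-test with noncentral t, d = 0.4, one-sided alpha 0.05 and power 0.95 needs n = 70 (attained power 0.952). With design effect DE = 1 + (NC − 1) × 0.1:

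- NC = 5: DE = 1.4; 70 × 1.4 = 98 people; 98/5 = 19.6, so 20 MSE.
- NC = 2: DE = 1.1; 70 × 1.1 = 77 people; 77/2 = 38.5, so 39 MSE.

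These match the article. Dividing by 25% completion gives 20/0.25 = 80 and 39/0.25 = 156 MSE at baseline, which is consistent with the stated recruitment range.

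**Step 2. When does the rule apply?** Only above 200 registrations: 200/1000 = 20% of exactly 1000 invited MSE, and a smaller share if more are invited.

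**Step 3. Power under the cap.** 200 × 0.25 = 50 completing MSE. Effective sample size = 50 × NC/DE.

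| Respondents per MSE | People at T2 | Effective n | Power at d = 0.4 |
|---|---|---|---|
| 5 | 250 | 250/1.4 = 178.6 | above 0.999 |
| 2 | 100 | 100/1.1 = 90.9 | 0.984 |
| 1 | 50 | 50 | 0.874 |

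With one respondent per MSE the plan's own target needs 70/0.25 = 280 MSE at baseline, more than the cap allows. With 300 registered and all analysed, 75 would complete and power would be 0.963. This case is not excluded: the plan says it cannot predict MSE size, and its penetration target is 50% or more, so two-person MSE at exactly 50% would give one respondent each.

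**Step 4. Precision lost.** With the same completion and cluster size in early and late registrants, the standard error scales with 1/√(number of MSE). The width of the capped interval relative to the full one is therefore:

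- 250 registered: √(250/200) = 1.118, about 12% wider; 50/250 = 20% of MSE discarded.
- 300 registered: √(300/200) = 1.225, about 22% wider; 100/300 = one third discarded.

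**The case against.** The strongest reply is that the rule will probably never apply. The plan foresees a low response and prepares for a shortfall, and more than one in five of 1000 invited MSE would have to register. A maximum set in advance also has a merit: nobody can decide afterwards how many late registrants to include. Both points stand. They make the matter less pressing, but they do not supply a reason for discarding data, and a closing date set in advance gives the same protection.

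A reader might infer three stronger claims that the document does not support.

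- **That the cap, with three quarters of MSE lost, leaves the study underpowered.** It does not in either stated scenario. The needs of 80 and 156 MSE already allow for that loss and lie below 200.
- **That the first 200 are a biased set of early adopters.** No section shows that early and late registrants differ, or that partners send their emails at different times. The back-up channels open only if the partner route falls short, so late registrants might come from another source, but that is a possibility and nothing more.
- **That adoption is capped at 20%.** This follows only if the rule governs adoption. The definition under Process outcomes counts all MSE registered at T0, and the capping sentence sits in a section about the primary outcome. The fair reading is that its scope is unclear.

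**Conclusion.** The point holds in a limited form. As written, the plan would drop usable data from eligible MSE by order of registration, with no stated reason, if more than 200 register. The certain cost is precision: intervals about 12% wider at 250 registrations and about 22% wider at 300, both totals being assumptions. The effect of selecting by order is unknown in size and direction. At the plan's 25% completion, the primary test keeps power of 0.98 or more for five or two respondents per MSE, and falls to about 0.87 against the planned 0.95 only at about one respondent per MSE. The rule is conditional and may never take effect, but the text is easily improved.

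**What to change.** Replace the capping sentence with one to this effect: *All eligible MSE registered by a prespecified calendar closing date will be analysed.* If the team wants it, report the result for the first 200 as a sensitivity analysis. Add that adoption and reach use all registrations, in line with their definitions under Process outcomes.

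Closing registration at a set number is not an equivalent remedy: closing at 200 would keep the same selection by order and would turn away later employers.

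The cost is slightly more analysis work and a final sample size that is not known in advance. No extra data collection is needed, since the platform already gathers the data.

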#### Analysis of quantitative data

To investigate the effectiveness of “System P”, the change in depressive symptoms between baseline and post-intervention assessment (T2) will be analyzed. Additionally, we will compare the change scores between individuals who completed a minimum amount of steps in the interventions (2 out of 3 steps for the PRA and 5 out of 7 steps in the SMT) and those who completed one step or less of the interventions. The effect evaluation will be performed with multilevel analysis, taking into account interdependencies at organizational level. For the quantitative process outcomes, we will calculate the average scores (e.g. for readiness for change) and average rates (e.g. penetration) and compare them across MSE with different socio-demographic characteristics.

#### Analysis of qualitative data

Qualitative data will be analyzed by transcribing the recordings and applying content analysis as described by Elo et al. [70]. It enables researchers to retrieve replicable and valid interferences with a dynamic categorization system. The initial categories will be based on the literature and the research questions (deductive approach) and can be expanded during the coding (inductive approach). Additionally, the category system and coding will be reviewed by two independent researchers. The results of the content analysis will also be summarized according to the Consolidated Framework for Implementation Research (CFIR) [71], which defines five main categories of determinants for successful implementation: (1) intervention characteristics, (2) outer setting, (3) inner setting, (4) characteristics of the individuals involved and (5) process of the implementation.

## Discussion

The study outlined in this paper aims to conduct a comprehensive evaluation of the implementation of stress prevention measures in MSE via the integrated web-based platform “System P”. “System P” combines a structural intervention (web-based tool for PRA) and behavioral intervention (web-based SMT) within a number of interactive features and additional information to overcome known barriers to stress prevention implementation. The analysis will include an effect evaluation and an extensive process evaluation to determine the success of the interventions under real-world conditions. Quantitative measurements will be complemented by qualitative data to gain more in-depth knowledge about the adequacy of the interventions and long-term success of the implementation. To the best of our knowledge, this will be the first implementation study for web-based stress prevention targeted at MSE.

One strength of the study design introduced is its variety in outcome measures. The success of the intervention is going to be assessed subjectively with standardized questionnaires filled in by employers as well as their employees, objectively by means of response rates, and also qualitatively by using interviews. This variety of measurement perspectives might help to foster the understanding of successful stress interventions in MSE.

Due to a restricted number of previous studies on the effectiveness of web-based tools for PRA, we are not sure about the expected effect sizes for the combined interventions. The present study design resembles an effectiveness-implementation hybrid design [46] which is considered a valuable alternative to the traditional research-practice divide in occupational health. The presented study can be classified as type 2 hybrid implementation research, whereby the evaluation of effectiveness and evaluation of the implementation process are of equal importance. This type of research considers established interventions in a new setting or target group, which in our case will be MSE. We hypothesize that a successful implementation process increases the effectiveness of web-based interventions for stress prevention. We also hope to identify additional drivers and barriers in the implementation process to adjust future interventions to the specific needs of MSE.

### Study limitations

One limitation of the study is the lack of a formal control group. Due to the high heterogeneity and low implementation rate among MSE, matching the enterprises adequately poses a major challenge. We will therefore compare those MSE who completed the necessary steps for the intervention with those who did not get far in their implementation process.

Another restriction lies in the chosen method of recruitment. The number of MSE registered with the cooperating recruitment partners is limited and the response rate to the invitation emails is likely to be low. In case we are unable to reach the required sample size for the implementation study with the proposed communication strategy, we will deploy a back-up strategy that includes alternative ways to recruit MSE. The project team will prepare target-group-oriented material for advertisements in magazines, social media campaigns, and personal recommendations to support the recruitment with or without the partners. Despite increasing the chances of successful recruitment, this unstructured communication strategy will restrict the opportunity to analyze adoption and reach of the implementation.

Even though we aim to reduce stigmatized terms and to promote the acceptance of work-related stress within the “System P”, the response behavior of the participants might be affected due to social desirability [72] and fear of stigmatization [73]. Talking about stress and mental health problems in the workplace is still a major challenge. In particular, employees may be concerned about negative consequences [74] and therefore may not answer honestly the online questionnaires or refuse to participate in the workplace check. Further, social desirability and the fear of stigmatization could lead to unexplained dropouts.

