The web-based training “GET.ON Stress” has already been evaluated showing significant effects on stress and stress-related problems like depressive symptoms as compared to controls [36–39]. It was designed to enhance two strategies of stress coping: problem-solving [40] and emotion regulation [41]. The training consists of seven sessions that participants should work on following a weekly schedule [36, 42] (see Table 2). Each session consists of general information, interactive exercises, prototype training participants – so called *personas*– who represent different stressed employee groups, quizzes, audio and video files and downloadable work sheets. In addition, at the end of sessions 2 to 6, users can choose to obtain extra information and perform short exercises about the following common stress-related topics: time management, rumination and worrying, psychological detachment from work, sleep hygiene, sleeping habit rhythm and regularity, nutrition and exercise, organization of breaks during work, and social support [42]. For this trial, we adapted “GET.ON Stress” to employees working at small businesses. Specifically, we adapted the personas within the web-based program who guide participants through the training. Personas are a well-established element of user-centered design in software engineering [43] that has also been used to tailor web-based interventions to specific target groups [44, 45]. Within “GET.ON Stress”, the personas aim to increase user engagement in the training, providing knowledge about how to complete the exercises within the training and helping users to transfer what they learn from the exercises into their daily lives; for instance, by giving examples of how employees working under similar circumstances apply a given problem-solving strategy in their daily life. Examples of the adapted personas for the MSE context can be found in Additional file 1. In addition to training content, participants can receive written feedback from an e-coach on their exercises after each training session. E-coaches are psychotherapists or master’s degree-level psychologists. Based on our experience from previous studies, we anticipate that the e-coaches will spend roughly 30 min per feedback. To improve the adherence of the participants with the training, the e-coaches will send reminders to participants any time they fail to complete a training session within 7 days. All communication between the participant and the e-coach will take place anonymously within the secured web-based platform “System P”. The duration of the intervention is completely self-paced (between 6 weeks and 6 months).

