## Part II -Effect and process evaluation of the web-based platform “System P”

### Study design

The presented study has a type 2 hybrid design for implementation research, evaluating the effectiveness and the implementation process of the intervention at the same time [46]. We will use a one-sample repeated measures design to evaluate the effectiveness of stress prevention via “System P”. Changes in mental health and work-related stress will be measured with the help of self-rated online questionnaires administered directly via the platform (see Table 3). Measurements will take place at baseline (T1), 6 months afterwards (T2) and 12 months after baseline (T3) (see Fig. 1). The primary outcome with regard to effectiveness will be the change in self-rated depressive symptoms between T1 and T2. Additional measurements for the process evaluation will take place between the assessment points [47], with semi-structured personal interviews between T1 and T2, and focus group interviews between T2 and T3. This study protocol describes the design of the pragmatic trial based on Standard Protocol Items: Recommendations for Interventional Trials (SPIRIT) guidelines [48] (see Additional file 2).

**Table 3 Tab3:** Quantitative measures and assessment points

Questionnaire	T1	T2	T3	NR
Socio-demographic variables (age, gender, family status, first language, education, occupational position, working hours, previous contact with mental illness, income, affinity for technology), 11 items	✓	–	–	✓
Information about the organization (staff headcount, history of health program use in the organization, location, occupational sector), 4 items	✓			✓
Patient Health Questionnaire (PHQ-8), 8 items	✓	✓	✓	
Perceived Stress Scale (PSS-4), 4 items	✓	✓	✓	
Irritation (subscale cognitive irritation), 3 items	✓	✓	✓	
Psychosocial Safety Climate (PSC-4), 4 items	✓	✓	✓	
Work demands and support (COPSOQ), 7 items	✓	✓	✓	
Sickness absence and productivity (Tic-P), 6 items	✓	✓	✓	
User experience, 11 items		✓		
Readiness for change, 3 items	✓	✓	✓	✓
Harms, 1 item		✓	✓	

Note: T1 = Baseline Assessment; T2 = Post-Implementation Assessment, 6 months after T1; T2 = Follow-Up Assessment, 12 months after T1; NR = Non-Responder Questionnaire, 1 month after T0

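### The comparison of completers with low users stands in for the missing control group, but use is self-selected after baseline; it should be labelled an exploratory dose-outcome association and reported with a baseline-adjusted analysis beside it

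*Protocol article*

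**What the plan says.** The Study design section states: "We will use a one-sample repeated measures design to evaluate the effectiveness of stress prevention". The primary effectiveness outcome is the change in PHQ-8 from T1 to T2 in the whole sample.

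The Study limitations section concedes: "One limitation of the study is the lack of a formal control group". It explains why matching enterprises would be hard and goes on: "We will therefore compare those MSE who completed the necessary steps for the intervention with those who did not get far". The word linking the two statements presents the comparison as the response to the missing control.

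The section Analysis of quantitative data gives the detail: "Additionally, we will compare the change scores between individuals who completed a minimum amount of steps in the interventions". The threshold is two of the three risk-assessment steps and five of the seven training sessions. The comparator is "those who completed one step or less of the interventions". Participants between the two limits fall in neither group. On method, the section says: "The effect evaluation will be performed with multilevel analysis, taking into account interdependencies at organizational level". It names no baseline score or other covariate for this contrast.

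Part I says of the stress management training: "The duration of the intervention is completely self-paced". It gives the risk-assessment cycle a length of 3 to 12 months, while T2 falls at 6 months.

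**The concern.** High and low users are not groups that the study forms. They arise after baseline from how far each participant or enterprise chooses to go. That choice can depend on symptoms at T1, motivation, workload and the kind of enterprise, all of which can also relate to how PHQ-8 moves over six months. A difference in change scores between the groups can therefore come from who completed and not from what the platform did.

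The study limitations cover recruitment, social desirability and stigma, but not self-selection or regression to the mean in this contrast. The Discussion also hypothesises that better implementation makes the interventions more effective, and this contrast bears directly on that. As the text stands, a selection-driven difference could be reported as the controlled evidence that the design otherwise lacks.

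**Working it through.** **1. The plan's own figures.** For a one-sample t-test with d = 0.4, one-sided alpha 0.05 and power 0.95, the noncentral t distribution gives n = 70 (achieved power 0.952). The design effect for five people per enterprise is 1 + (5 − 1) × 0.1 = 1.4, so 70 × 1.4 = 98, and 98/5 = 19.6, or 20 MSE. For two per enterprise it is 1.1, so 70 × 1.1 = 77, and 77/2 = 38.5, or 39 MSE. All stated figures reproduce. They size the overall change only, not the comparison of use groups.

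**2. Inputs for the bias.** The documents give neither the baseline gap g between use groups (in T1 SD units) nor the T1–T2 correlation r. Assumed ranges: g = 0.3 to 0.5 and r = 0.5 to 0.7.

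**3. Case A: the gap is transient, and there is no intervention effect.** Both groups follow one regression line, T2 = r × T1 + noise, with equal variances. If completers start g higher, their T2 mean is r × g higher. The difference in mean change is r × g − g = −(1 − r) × g, an apparent extra improvement of (1 − r) × g.

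| g | r = 0.7 | r = 0.5 |
|---|---|---|
| 0 | 0 | 0 |
| 0.3 | 0.09 | 0.15 |
| 0.5 | 0.15 | 0.25 |

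If completers start lower, the sign reverses and a real benefit would be masked.

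**4. Error rate in case A.** A simulation with no true effect used 3000 runs, n = 98 split 49/49 or 25/73, clustering ignored, and a two-sided 5% test. The change-score test rejected in about 8–12% of runs at g = 0.3 and 13–23% at g = 0.5. With T1 as a covariate, rejection stayed at about 4–6%. At g = 0 both tests were near 5%. The data were generated under case A, where baseline adjustment is correct by construction, so this does not show that adjustment is right in general.

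**5. Case B: the gap is stable, and there is no intervention effect.** Each group regresses to its own mean, so T2 means also differ by g and the change-score difference is g − g = 0. A model adjusted for T1 with within-group slope r now gives g − r × g = (1 − r) × g, the same 0.09 to 0.25 SD. It makes completers look worse if they started higher.

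**6. Reading A and B together.** The two analyses err under opposite assumptions and, for a given gap, in opposite directions. Neither is safe alone for self-selected groups. Agreement between them makes the baseline gap a less likely explanation; disagreement means that the data cannot settle the question.

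**The case against.** The strongest reply is that the contrast is secondary. It is introduced as an addition, the sample size does not rest on it, and a fault in it leaves the primary overall change untouched. That stands, and it limits the severity.

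A reader might also infer more than the document supports:

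- **That the contrast will show a spurious benefit.** The document gives neither the size nor the direction of any baseline gap. The bias can be zero, can favour the platform or can hide an effect.
- **That the analysis certainly has no covariates.** The article names only clustering, but a fuller plan, not shown, may add some. The point rests on how the contrast is presented, not on a missing covariate list.
- **That adjustment for T1 should replace change scores.** Case B shows that adjustment brings its own bias when group differences are stable (Lord's paradox).
- **That the bias is a given share of the planned d = 0.4.** That d refers to a mean change in one sample. The figures here are differences between groups in baseline SD units, so a ratio of the two is not like for like.
- **That low users will largely have no T2 score.** The Sample size section reports that "only one quarter of all MSE that start interventions for stress prevention complete them", and 20/0.25 = 80 and 39/0.25 = 156 are consistent with its recruitment goal. But it also says that completion of T2 cannot be predicted, and nothing restricts the T2 questionnaire to users. Selective T2 response is a possibility to report, not an established fact.

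A long covariate list would also be too heavy for about 98 people in about 20 enterprises.

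**Conclusion.** The point holds as a should-fix. The article offers a comparison of self-selected use groups as its response to having no control group, fixes it on change scores, and attaches no warning about selection. The bias can run either way. Where the baseline gap is transient, it is 0.09 to 0.25 baseline SD for gaps of 0.3 to 0.5 SD and correlations of 0.5 to 0.7. All of these inputs are assumptions, and without a gap this component is zero. What needs correcting is the claim that the contrast may carry, together with a check that would expose its dependence on baseline differences.

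**What to change.** In both Analysis of quantitative data and Study limitations, state that the comparison of use groups is an exploratory dose-outcome association, not a substitute for a control group and not evidence of a causal effect. Then:

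1. Define use by steps completed up to T2, so that later activity does not decide the group for a T1–T2 change.
2. Report T1 characteristics by use group.
3. Beside the change-score contrast, report a multilevel model of T2 PHQ-8 adjusted for T1 PHQ-8 and a short prespecified set of T1 variables already in Table 3, for example occupational position, headcount and readiness for change.
4. Interpret the result only where the two analyses agree, and note that unmeasured confounding and selective T2 response remain in both.

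No new data are needed. The cost is a weaker permitted claim and one extra analysis. The primary analysis is unchanged.
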